### Cost-effectiveness analysis

To determine the outcome measure for use in cost-effectiveness analysis, the main assumption will be that there is a link between ART adherence and viral load. If this assumption be true, then cost-effectiveness analysis will utilize viral load (VL) as the primary outcome.

This primary outcome will be mapped on to long-term outcome measures—QALY/DALY as the data may permit, using models such as WHO-CHOICE and or WHO DALY/QALY estimators, to generate cost-effectiveness (47). Appropriate adjustments, including inflation, exchange rate, and discounting for costs and outcomes shall be conducted.

The WHO-CHOICE (Choosing Interventions that are Cost-Effective) and DALY/QALY (Disability-Adjusted Life Years/Quality-Adjusted Life Years) estimators are two tools developed by the World Health Organization (WHO) to help evaluate the cost-effectiveness of healthcare interventions. The WHO-CHOICE estimator is a tool that calculates the cost-effectiveness of healthcare interventions based on their impact on disease burden and their cost. It uses a standardized approach to estimate the costs and health outcomes of different healthcare interventions, taking into account the local context of each country. The estimator is designed to be flexible and can be adapted to different healthcare settings and disease profiles.

The WHO DALY/QALY estimator is a tool that measures the burden of disease and the impact of healthcare interventions on health outcomes. It uses a measure called Disability-Adjusted Life Years (DALYs) or Quality-Adjusted Life Years (QALYs) to quantify the impact of disease on individuals and populations. DALYs and QALYs take into account both the years of life lost due to premature death and the years lived with disability or illness. The WHO DALY/QALY estimator can be used to evaluate the cost-effectiveness of healthcare interventions by comparing the cost per DALY or QALY gained. Both WHO-CHOICE and DALY/QALY estimators are widely used by policymakers, healthcare providers, and researchers to help make informed decisions about allocating healthcare resources and designing cost-effective healthcare interventions.

To determine cost-effectiveness of the service delivery models, we will compare the measures determined with conventional benchmarks such as Gross Domestic Product (GDP) per capita, or will compare with literature from other but similar contexts. Throughout the study we will apply the guidelines for economic evaluation from the second panel on cost-effectiveness (48) and the recommended CHEERS guidelines for reporting the results (49).

### Ethical considerations

The study protocol will be presented to the relevant institutional review boards. Every participant will be reimbursed transport costs based on the rate for the furthest participant and refreshments will be served after focus group discussions and group support sessions. LHWs facilitating the group sessions will receive a financial incentive equivalent to 2.72USD per session.

Group support psychotherapy is offered as a continuous service at the Kitgum general hospital. All study participants will have access to GSP if found to be highly beneficial in improving ART adherence and viral suppression. This trial is registered with The Pan African Clinical Trials Registry Number PACTR202006601935462.

## Results

### Trial status

The trial has been approved by the Makerere School of Health Sciences Research Ethics Committee, and the Uganda National Council of Science and Technology. Recruitment began in June 2021 and closed October 2021. A total of 120 young people (10–18 years) living with HIV with their adult caregivers were recruited into the trial. They were randomized to receive the adolescent group support psychotherapy (A-GSP) and intensive adherence counseling (IAC) (*N* = 61) and IAC alone (*N* = 60). An analysis of baseline, 6 and 12-month data is in progress. The results of this trial will be presented at national and international conferences. Manuscripts will be prepared for publication in peer-reviewed journals and reports will be prepared for submission to the funding agency.

## Discussion

The mental health needs of young people living with HIV have been documented in high income countries, but remain underexplored within low and middle income countries (50). The negative consequences of poor mental health, in particular, depression include poor adherence to ART, poor service engagement, and risk behaviors (51). Unfortunately, recent systematic reviews indicate a dearth of psychological interventions for these mental health issues, therefore, affected individuals continue to experience high morbidity and mortality rates especially within low and middle income countries (52).

To our knowledge, this is the first trial to examine the feasibility, acceptability and preliminary effectiveness of a psychological intervention-GSP on ART adherence and viral suppression among young people living with HIV in sub-Saharan Africa. Through qualitative research prior to the trial, the GSP model will be adapted to suit the needs of young people (10–18) years and will be delivered using play materials. Play therapy allows children to utilize toys and other play materials to express their own story and emotions without necessarily using words to participate in the counseling process (53). Play therapy has been shown to produce outcomes that are as effective as traditional talk-therapy methodologies commonly used with adult populations (54).

Given our prior research findings which indicated that GSP improved viral suppression through sequential reduction in depression symptoms and improvement in ART adherence (21), in this trial we selected those young people who had failed to suppress the HIV virus after 6 months of ART use. We assume this category of young people is more likely to have mental health challenges like depression which are amenable to GSP. We hypothesize that remission of depression would then lead to motivation to take ART and improve viral suppression. However, reduction of depression in of itself has been shown to improve viral suppression in our adult HIV study samples (21). Prior studies have shown that reduction in ANS activity brought about by reduction in stress inhibits HIV viral replication (55, 56). This pilot trial provides an opportunity to replicate these associations among young people living with HIV.

### Potential impact and significance of the study

Mental health problems such as depression largely affect ART adherence which is critical to the success of viral suppression among young people living with HIV (57, 58). There is a dearth of mental health interventions to improve HIV treatment outcomes in young people living with HIV (59). This trial evaluates the feasibility and preliminary effectiveness of a psychological intervention in improving ART adherence and viral suppression. Further, the trial will provide an opportunity to explore mechanisms that affect HIV treatment adherence and viral suppression, which could be exploited to improve HIV treatment outcomes in other low resource settings. Further, the trial will provide evidence for scale up of GSP in both young and adult populations with HIV in low resource settings.

### Limitations

This study has several limitations. First, the study will include only 120 participants from five community based HV clinics in one northern Uganda district. Our results may not be generalizable to other areas in Uganda. Second, study participants will reside in similar villages attending similar HIV clinics, thus the chances of contamination are high which may result in non-detection of significant differences when they truly existed. However the major goal of this trial is to determine feasibility and acceptability of study procedures in preparation of a definitive trial in the near future. Further, in view of the small number of mental health workers trained in delivering GSP using play materials, supervision of treatment sessions was not possible. Also, the limited numbers of diploma and degree-level health workers restrict the long term accessibility and sustainability of GSP among young people. Future research will assess whether or not the intervention can be administered by lay health workers.

## Conclusions

Successful completion of this trial will pave way for a definitive cluster randomized trial that can critically inform the national dissemination and implementation of GSP to improve HIV treatment outcomes in young people living with HIV in low resource settings.

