**Methods:**

We recruited 120 young people with HIV, aged 10–18 years, who had non-viral suppression 6 months after initiating first-line anti-retroviral therapy (ART) from community based HIV clinics in Kitgum district, northern Uganda. Participants were randomly assigned to receive GSP plus IAC (*N* = 60) or IAC alone (*N* = 60). Primary outcomes will be indicators of feasibility and acceptability as well as preliminary effectiveness of GSP in improving ART adherence and viral suppression analysed by intention to treat using cluster-adjusted t tests and permutation tests. Secondary outcomes will be measures of depression, anxiety and cost-effectiveness.

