The goal of this paper is to describe the protocol for the evaluation of the feasibility, acceptability and preliminary effectiveness of group support psychotherapy in improving ART adherence and viral suppression among HIV positive young people in Uganda. In the preparatory phase of this trial, we aim to conduct community-based participatory qualitative research to obtain information on the potential usefulness of group support psychotherapy in addressing the psychosocial challenges that impact adherence to anti-retroviral therapy and viral suppression among young people with HIV in northern Uganda.

In the trial phase of this study, the primary objective will be to assess the feasibility, acceptability and preliminary effectiveness of GSP in promoting ART adherence and viral suppression among HIV positive young people with non-viral suppression 6 months after initiating first-line ART at community-based HIV clinics in Kitgum district. Secondary objectives will include exploration of indicators of causal mediating processes and contextual influences, exploration of whether or not improvement in psychosocial challenges including depression, posttraumatic stress symptoms, suicide risk, social support, and stigma mediate or modify the effect of GSP on ART adherence and viral suppression, exploration of whether or not promotion of adherence through group support psychotherapy translates into better viral load suppression compared to standard care with intensive adherence counseling (IAC) and exploration of the cost-effectiveness of GSP to improve viral load suppression among HIV positive young people taking anti-retroviral therapy.

We hypothesize that in comparison to the control intervention, GSP will demonstrate better feasibility, acceptability and better preliminary HIV treatment outcomes and better cost-effectiveness. The primary end point will be 6 months after the end of the intervention. Data will be used to design a definitive cluster randomized trial which will test the hypothesis that group support psychotherapy promotes better ART adherence and viral suppression than standard care with intensive adherence counseling among HIV positive young people with non-viral suppression 6 months after initiation of first-line ART in Uganda.

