**Primary outcomes**					
Indicators of feasibility	The proportion of eligible participants who take up either intervention (**Reach**) The proportion who attended all 8 sessions of either intervention (**Dose delivered**) The proportion who are lost to follow-up (**Attrition**) will be determined from the attendance registers		✓		
Indicators of acceptability	A 9-item questionnaire (34) will assess participant's satisfaction, the group facilitators’ knowledge and attitudes, and the participant evaluation of the intervention's ability to reduce stress		✓		
Adherence to ART	One question “During the past three weeks, on how many days have you missed taking all your medication doses?”	✓		✓	✓
Viral Load	Medical charts of study participants	✓		✓	✓

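### The pilot frames and tests GSP feasibility and acceptability as superiority over IAC, which ignores the absolute levels that its main question needs

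*Protocol article*

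**What the plan says.** Under Limitations, the article states that "the major goal of this trial is to determine feasibility and acceptability of study procedures in preparation of a definitive trial". The Abstract agrees: "Primary outcomes will be indicators of feasibility and acceptability as well as preliminary effectiveness of GSP".

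Table 2 defines the feasibility indicators as proportions:
- reach: "The proportion of eligible participants who take up either intervention"
- dose delivered: "The proportion who attended all 8 sessions of either intervention"
- attrition: the share lost to follow-up.

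Acceptability is a 9-item questionnaire. The article attaches no target level to any of these.

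The stated expectation is comparative: "We hypothesize that in comparison to the control intervention, GSP will demonstrate better feasibility, acceptability and better preliminary HIV treatment outcomes". The Abstract assigns the primary outcomes, feasibility and acceptability included, to cluster-adjusted t tests and permutation tests under intention to treat. The Quantitative data section describes collapsing 120 participants to 12 group summaries and comparing cluster means between arms. No other quantitative analysis is given for the feasibility indicators.

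On what follows the pilot, the Introduction says "Data will be used to design a definitive cluster randomized trial", and the Conclusions say "Successful completion of this trial will pave way for a definitive cluster randomized trial".

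**The concern.** Whether GSP can be delivered, and whether a trial can keep young people and caregivers to its endpoint, are questions about levels. A between-arm difference does not answer them. If attendance is poor in both arms but less poor under GSP, the hypothesis is confirmed. If attendance is excellent in both arms, it usually is not. The test result can then be read as the answer to the pilot's main question when it answers a different one.

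The dose indicator sharpens this. It counts attendance at all eight sessions of either intervention. The section on standard of care describes IAC as at least four sessions, while Table 1 sets out three with a fourth that depends on the adherence score. These passages must be reconciled. If few IAC participants can reach eight sessions, GSP looks better on dose almost by construction.

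**Working it through.** **The plan's own figures.** The 60 per arm comes from a cited rule of thumb (Sample size justification) with no alpha, power, effect or precision, so no formula reproduces it. The arithmetic agrees: 2 × 60 = 120, and 120/12 = 10 per group, within the stated 10–12. An equal split gives 6 v 6 groups of 10.

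**Assumptions.** The article gives no expected feasibility rates and no ICC. All rates below are assumed, and ICC is taken as 0 to 0.10. The test is a two-sample t test on group means, two-sided 5%, counted when it favours GSP, with 10 degrees of freedom and critical value 2.228.

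**Formula.** With true proportions a (GSP) and b (IAC), and m = 10:
- variance of a group mean: v = [(a(1−a) + b(1−b))/2] × (1 + 9·ICC)/10
- standard error of the difference: SE = √(2v/6)
- non-centrality: (a − b)/SE, referred to a non-central t.

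**Worked case, 40% v 20%.**
- ICC 0: v = 0.20/10 = 0.020; SE = √(0.040/6) = 0.0816; non-centrality 0.20/0.0816 = 2.45; probability 0.60.
- ICC 0.10: v = 0.020 × 1.9 = 0.038; SE = 0.1125; non-centrality 1.78; probability 0.36.

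**Results.** The rows for 95% v 95%, 90% v 95% and 50% v 25% at ICC 0 are from simulated binomial group means (20,000 runs). The others use the formula.

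| GSP v IAC (assumed) | Finds GSP better, ICC 0 | ICC 0.10 |
|---|---|---|
| 95% v 95% | 2.6% | about 2.5% |
| 90% v 95% | 0.2% | not computed |
| 85% v 80% | about 10% | about 7% |
| 40% v 20% | 60% | 36% |
| 50% v 25% | 74% | 48% |
| 40% v 5% (few IAC participants reach eight sessions) | 99.5% | 91% |

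With a single GSP level of 40%, the ICC 0 result moves from 60% to 99.5% when only the IAC rate changes. The test does not track how well GSP was delivered.

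**What the existing sample says about levels.** Exact 95% intervals for 60 GSP participants, ignoring clustering:
- 24/60 (40%): 28% to 53%
- 51/60 (85%): 73% to 93%.

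These do not overlap. At 80%, the approximate half-width is 1.96 × √(0.8 × 0.2/60) = 10 points at ICC 0, and 1.96 × √(0.8 × 0.2 × 1.9/60) = 14 points at ICC 0.10. So 60 per arm separates poor from good feasibility in absolute terms, even with some clustering.

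**The case against.** The strongest reply is that the levels are already there. Table 2 defines the indicators as proportions, so they will be reported. The sentence in the Abstract groups feasibility with effectiveness before it names the tests, so it may not mean that feasibility is judged by a test alone. This stands in part. But the comparative hypothesis is printed, and the article gives no other quantitative analysis for these outcomes.

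A reader might infer more: that going on to the definitive trial hangs on mere completion, or on GSP beating IAC, so that a workable programme could be refused. The documents do not support this. The sentence in the Conclusions is a closing remark that leaves the word successful undefined. No section ties progression to the hypothesis, so a workable GSP could fail the hypothesis but not progression. The Introduction and the Sample size justification also say that the pilot data will inform the design of the later trial, so one cannot say that the results have no power to reshape it.

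Nor is the lack of go/amend/stop limits a fault by itself. This is a condensed article, and limits may sit in the full protocol.

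On the numbers, 2.6% at 95% v 95% is simply the one-sided error rate of the test, and the 40% v 20% case builds in a true doubling. Both remarks are fair. They also restate the point: the test responds to the difference, whatever the level. Giving the workable case a true GSP advantage (85% v 80%) still yields only about 10%.

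**Conclusion.** The concern holds in a limited form. The hypothesis and the only stated test for the primary feasibility and acceptability outcomes are comparative, while the pilot's main question is absolute. Poor delivery in both arms can confirm the hypothesis (60% of the time at 40% v 20% with ICC 0, 36% with ICC 0.10), and excellent delivery in both usually cannot (2.6% at 95% v 95%). These sizes rest on assumed rates, an equal 6 v 6 split and groups of 10, so they illustrate the mismatch and do not forecast this trial. The mismatch itself depends on none of them. It should be corrected because it bears on the stated major goal and the remedy is cheap. It does not show that the decision to proceed is mis-specified.

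**What to change.** In the Introduction, replace the hypothesis of better feasibility and acceptability with absolute estimation. Report dose delivered and satisfaction for the GSP arm, and uptake and retention for the trial as a whole, each with a 95% confidence interval that allows for clustering. Judge feasibility on these, against any limits already fixed in the full protocol.

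If limits are set only now, date them and disclose which results have been seen. Trial status says that analysis of the baseline, 6- and 12-month data is under way, and Table 2 schedules the feasibility measures at month 2, so new limits may be post hoc.

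Treat between-arm feasibility differences as descriptive, and reconcile the eight-session dose indicator with the described number of IAC sessions. Keep the between-arm tests for adherence and viral load.

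The cost is wording and a short analysis, with no new participants or data. The downside is that the sponsor gives up a comparative feasibility claim and may have to report poor absolute feasibility.
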